#### Sample size calculation

3.3.1

The calculated sample size is 571 mother–child pairs. Our main objective is to investigate the effect of early-life exposure to air pollution on child growth/development. Stunting, a prevalent manifestation of chronic malnutrition, is one of the significant indicators for delay in the achievement of growth/developmental milestones in children (47). Hence, we have calculated the sample size by assuming a power of 80%, a two-sided confidence level of 95%, and by using data available from a recent publication (48). This article estimated an odds ratio (OR) of 1.74 for stunting among under-five children with long-term exposure to PM_2.5_. We applied relevant continuity correction and inflation to account for participant exclusions during follow-up and anticipated non-response/participant attrition. Thus, we will enroll 783 pregnant women in each study city (1,566 participants in total) to establish the final cohort of 571 mother–child pairs. Further details of sample size calculation have been enumerated in Supplementary material (Data Sheet 2). We will continue to use the same cohort for our subsequent objectives.

#### Sampling strategy

3.3.2

We will obtain information about eligible pregnant women in the study area from community health workers (CHWs), who are usually the first point of contact for antenatal care (ANC) among Indian pregnant women (49, 50). Before the launch of the study, we will identify and enlist, with the help of relevant district-level offices, all the CHWs working in both study cities under the Integrated Child Development Scheme (ICDS) and National Health Mission (NHM) (51, 52). These include Anganwadi workers (AWW) and Accredited Social Health Activists (ASHA), respectively (49, 50). We will approach all CHWs to gain their consent to cooperate, and those willing will be briefed about the study participant enrollment procedure.

We will contact pregnant women identified by CHWs at their homes or at the nearest Anganwadi Centre [community maternal and child care centre in India functioning under the ICDS (53)] to describe our study, confirm their eligibility using a pre-designed checklist, and finally obtain written informed consent. After administration of written informed consent (including consent for follow-up of their child for one year), pregnant women will be enrolled for participation in the study.

### Data collection

3.4

#### Exposure data collection

3.4.1

A multi-pronged strategy will be used to collect individual and neighborhood-level exposure data. To begin with, historical data on the neighborhood-level concentration of air PM (PM_10_ and PM_2.5_) covering the two study cities will be retrieved from available open-access sources. For example, in India, in addition to using satellite-derived aerosol optical depth as a source for PM data, the Central Pollution Control Board (CPCB) provides freely available information from its network of fixed-site automatic monitors (continuous ambient air quality monitoring stations - CAAQMS) and gravimetric samplers under the National Air Quality Monitoring Program (NAMP) (54, 55). Using the city-level air PM data, we will develop an exposure database at a high spatial scale using the Land Use Regression (LUR) model for both cities. LUR has been widely used to predict the concentration of air pollutants (measured through distant fixed site monitors and/or remote sensing data) at target locations (i.e., the residential addresses of the selected participants) (56–58). We will develop our LUR model to assign ambient PM_2.5_ and PM_10_ exposure to each participant based on the geocodes of their residence. We will follow the methodologies previously published for urban area LUR models, such as that under the ESCAPE project (59) and for Indian cities (60, 61). Accordingly, in our LUR model, we will use data for a range of geographic, population, and emission source-specific predictor variables retrieved from open access sources, including satellite data, local authorities, and/or collected from field-level verification. For example, data on land use, road network, population density, elevation, meteorological, and other relevant variables will be used, in line with previous studies (56–58). We will adopt a supervised forward addition linear regression approach for model development and perform diagnostics on the fitted models to maintain the linear regression. Finally, we will assess the performance of the developed model by adopting a 10-fold cross-validation approach (62). In addition, we will also measure the personal exposure to air PM (PM_10_ and PM_2.5_) of each enrolled pregnant woman once in each trimester after enrolment to increase the accuracy of PM exposure data while accounting for participant mobility. For these measurements, low-cost battery-operated portable sensors will be used, as has been reported in previous studies (63, 64).

For the heavy metal component of our study, we will conduct biomonitoring of study participants. Blood samples collected from enrolled pregnant women and their live-born children will be analyzed through Inductively coupled plasma optical emission spectroscopy (ICP-OES) using the hot-acid digestion method given by the United States Environmental Protection Agency (USEPA) (65). We will limit our analysis to those heavy metals that are known to adversely affect childhood growth and development and are found in the ambient air of study cities during our air sampling and subsequent composition study. For this, we will refer to previous large-scale studies conducted in Spain, China, and other countries, as well as published systematic reviews (66–70), to compile a list of heavy metals with known adverse effects on childhood growth and development. Simultaneously, we will conduct air PM composition analysis focussing on identifying heavy metals that exceed the permissible limits in the ambient air following CPCB methodology (71) for sampling and, subsequently, USEPA guidelines for laboratory analysis (65).

#### Outcome and covariates data collection

3.4.2

##### Pregnant women

3.4.2.1

In the first (baseline) visit to households of eligible and consenting pregnant women, the detailed residential address (including contact details and geographic coordinates), as well as details of the participant and her household members, will be collected at the time of enrolment. Briefly, we will collect information on age, education, occupation, lifestyle factors, medical history (including details of current/past pregnancy and prescription drug use), and relevant family history from the pregnant women. The maternal height and weight will be recorded at the baseline visit. Detailed data about previous pregnancies (if any) will include parity status, birth intervals between consecutive births, and history of anemia/malaria/urinary tract infection/other infections/any other complications in a past pregnancy. In addition, the demographic details, socioeconomic characteristics, water, sanitation, hygiene, and environmental factors related to her household will be collected. The enrolled pregnant women will be followed up once in each trimester in the remaining period of gestation to collect information regarding the occurrence of spontaneous abortion/miscarriage and the details of scheduled antenatal check-ups undergone by the pregnant women. We will note their preference for a hospital/healthcare facility where they would opt for childbirth.

##### Live-born children

3.4.2.2

###### Early neonatal period

3.4.2.2.1

According to the information regarding the calculated expected date of delivery (EDD) obtained during the baseline visit, the pregnant women will be contacted within 1 week of the EDD to collect information on pregnancy/birth outcomes (date of childbirth to calculate the child’s chronological age, live birth versus stillbirth, gestational age at birth and congenital anomalies). After getting information about the birth, study staff will visit the hospital/house of the mother to collect anthropometric data of the baby (preferably within 72 h of birth) to supplement the information obtained from hospital/medical records. In cases where the mother/child cannot be contacted within 72 h of birth, we will try to collect relevant data about the child as early as possible before the 1st-month follow-up visit.

###### Monthly follow-up of the child till 1st year of age

3.4.2.2.2

All eligible live-born children will be followed up at their homes/nearest Anganwadi centre. To ensure timely and smooth data collection, follow-up visits will be scheduled in a manner that these visits coincide with routine house-to-house visits carried out by CHWs under different ongoing national programs [such as Home-based newborn care (HBNC) and Home-Based Care for Young Child Programme (HBYC) under NHM and “Poshan Abhiyan” (72), “Dastak Abhiyan” specific to MP (73)]. In each monthly follow-up visit, anthropometry, achievement of developmental milestones, and acute morbidity profile will be recorded. Additional information about at-birth APGAR score, weight, length, head, and mid-arm circumference will be collected in the 5th visit (child age 1 month). Blood samples for heavy metal analysis and the data on child immunization and feeding practices will be collected in the 17th visit (during the 12th month of the child’s age).

##### Details of data to be collected

3.4.2.3

The list of domains, variables, and measurement timing of this study are described in subsequent paragraphs and shown in Figure 1.

###### Exposure variables

3.4.2.3.1

The main exposure/independent variables to be investigated in this study are mean (daily/monthly/annual) concentration of particulate matter (PM_10_ and PM_2.5_) for the specific geo-location of each study participant and mean levels of heavy metal in blood samples of participants (pregnant women and children).

###### Study outcomes

3.4.2.3.2

The primary study outcomes are related to childhood growth and development, as shown in Tables 1, 2. In addition, we will also estimate the incidence rate of ARIs (number of episodes of ARI during infancy/total number of children under follow-up). We modified the Integrated Management of Childhood Illness definition for ARI [given by WHO/UNICEF (74)] which has been used previously (75) to create an operational definition of ARI for this study. Modification was done by incorporating the signs and symptoms mentioned in the Integrated Management of Neonatal and Childhood Illness (IMNCI), Ministry of Health & Family Welfare, Government of India. Accordingly, ARI will be defined as cough or difficulty in breathing with or without any general danger signs, with or without any chest indrawing, stridor, and fast breathing. Depending upon the site of inflammation determined by the paediatrician based on clinical signs and symptoms, it will be classified as ARI of the upper respiratory tract and ARI of the lower respiratory tract. Further, depending upon the severity, ARI will be classified as per IMNCI guidelines into “No Pneumonia: cough or cold,” “Pneumonia,” and “Severe Pneumonia or Very Severe Disease.” Based on previous research, we will define each episode of ARI to last for two weeks (75). When a child who has had no symptoms for at least one week develops signs and symptoms of ARI, we will treat that as a new episode (75).

**Table 1 tab1:** Operational definitions, indicators, and measurement methods to be used for child growth-related outcome measures.

Outcome	Operational definition	Variable/indicator	Measurement method
Small for gestational age (SGA)	As per the WHO definition of SGA given by the 1995 WHO expert committee, infants having a birth weight for gestational age below the 10th percentile based on a sex-specific reference population (139, 140).	Proportion of children diagnosed as SGA at birth (proxy of in-utero growth of the child)	Based on hospital records-verified by study staff
Low birth weight (LBW)	Infants with a birth weight of less than 2,500 g, regardless of gestational age at the time of birth (141, 142).	The proportion of children diagnosed as LBW at birth (proxy of in-utero growth of the child)	Based on hospital records-verified by study staff
Overweight/ obese	Children’s body mass index (BMI - calculated as weight in kilograms divided by height in metres squared) will be plotted on WHO BMI charts and those with a BMI above the 95th percentile will be classified as obese and overweight will indicate those children whose BMI falls between the 85th and 95th percentile (143, 144).	The proportion of overweight/obese (based on BMI for age) infants at the end of the first year of life.	Monthly measurement of height/length, weight, and calculation of BMI
Underweight, wasted and stunted	*Z*-scores for growth indicators (length/height-for-age, weight-for-age, weight-for-length/height, BMI-for-age) will be estimated by comparing each child’s height/length and weight with WHO growth standards as shown in the image below (which has been adapted from the WHO child growth standards: training course on child growth assessment) (145). Based on where their calculated z-scores lie with respect to the median value of the standard reference population, children will be categorized as: Underweight: ‘weight for age’ below minus two standard deviations (-2SD) Severely underweight: ‘weight for age’ below minus three standard deviations (-3SD) Stunted: ‘height/length for age’ below minus two standard deviations (-2SD) Severely Stunted: height/length for age’ below minus three standard deviations (-3SD) Wasted: ‘weight for height/length’ below minus two standard deviations (-2SD)	Proportion of children with abnormal Z-scores for afore-mentioned growth indicators (i.e., underweight, severely underweight, stunted, severely stunted, wasted and severely wasted) at the end of the first year of life.	*Z*-scores for growth indicators (length/height-for-age, weight-for-age, weight-for-length/height, BMI-for-age) obtained from comparison of each child’s height/length and weight with WHO growth standards

**Table 2 tab2:** Operational definitions, indicators, and measurement methods to be used for child development-related outcome measures.

Outcome	Operational definition	Variable/Indicator	Measurement method
Development progress	The developmental level of the child will be assigned a score ASQ-3 (146, 147). ASQ-3 has been widely used in many countries as a field-based parent-completed screening tool to assess five developmental domains (148). It has also been previously used and validated in the Indian population (149, 150).	Domain-specific and mean score of ASQ-3 obtained monthly	Ages and stages questionnaires- third edition (ASQ-3) questionnaire (146, 147)
	Developmental Quotient (DQ) is calculated by dividing Developmental Age by Chronological Age and multiplying it by 100 (151, 152). Developmental Age (DA): Each child will be assigned a DA at each follow-up visit for each of the 5 developmental domains, i.e., gross motor, fine motor, adaptive/cognitive, language and personal-social developmental domains. Study staff under the supervision of a paediatrician will estimate DA according to the achievement of domain-specific developmental milestones. Chronological Age (CA): the actual age of the child calculated from his/her date of birth	Proportion of children with delayed achievement of development milestones at the end of the first year of life. Domain-specific monthly developmental level of each infant obtained through Development quotient calculation	Questionnaire developed by authors and pilot-tested in an ongoing built environmental child cohort (84)

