### Statistical analysis and reporting

3.6

The data will be entered using open access online applications from which the data will be downloaded and exported to SPSS statistics software (Version 25) and the latest versions of R packages/R studio for analysis. Data will be summarized using descriptive statistics like mean/standard deviation (SD) or median/Interquartile range. For categorical variables, summary estimates will be reported using frequency with percentages and within two selected study settings. An initial analysis will compare aggregated data between cities with high and low pollution levels. For this, relative risk (RR) and attributable risk (AR) will be calculated through the relevant equations using the probability of outcome (incidence/proportion) among the high pollution group (exposed) divided by the probability of outcome among the low air pollution group (relatively unexposed).

The next level of analysis will be based on the range of the estimates of PM_2.5_ /PM_10_ exposure concentrations and blood heavy metal levels found in the study participants (i.e., pregnant women/live-born children). We will use relevant correlation coefficients to assess possible correlations between environmental variables- PM2.5 /PM10/blood heavy metal levels and the health outcomes – growth indicator related z scores/development quotient/ARI episodes (Pearson or Spearman).

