Finally, multivariable logistic regression model analyses will be used to study the relationship between environmental variables- PM_2.5_ /PM_10_/blood heavy metal levels and the health outcomes in binary forms – growth/development/ARI. Briefly, multiple linear mixed-effects regression model analyses will be used to study the relationship between the levels of early-life exposure (concentration of environmental pollutants- PM_2.5_ /PM_10_ concentration/ heavy metals in pregnant women and the child participant- monthly means for the former and cumulative mean- i.e., in-utero maternal exposure summed with infancy period exposure to heavy metal) and child health outcomes- mean anthropometric data (height, weight, head, and mid-arm circumference) and developmental level (obtained from developmental quotient/mean score on ASQ-3 scale) of each participant (live-born children) while adjusting for confounders. Similar regression equations will be used to analyze the association between exposure and delay in achieving growth and developmental milestones. Subsequently, the PM_2.5_, PM_10_ data and other environmental/sociodemographic data will be used in a logistic regression model of ARI symptoms within a distributed lag nonlinear modeling framework (DLNM) (88, 89). This approach will test the associations of PM_2.5_ /PM_10_ exposure over the preceding time periods and the distribution of growth z-scores / occurrences of ARI events (90–92).

Analyses will be performed separately for each child’s morbidity outcomes, such as growth/developmental parameters/domain. All analyses will adjust for different confounding variables included in the study. Details of such confounders for statistical adjustment will consist of gender, family size, socioeconomic status, gynecological/obstetrics/other relevant medical history, and data from environmental assessments of the households (built environmental attributes). We will also adjust for the effect of low birth weight and small-for-gestational-age on the studied association (Supplementary material). We will also conduct sensitivity analyses to test the robustness of our findings, for example, analysing a subset with complete data and comparing the results with the entire dataset where missing data imputations have been done.

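### The ARI incidence rate is defined per child rather than per child-time, incidence is then treated as a probability, and no adjusted model named in the article estimates a rate

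*Protocol article*

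**What the plan says.** Section 3.4.2.3.2 (Study outcomes) names growth and development as primary and adds ARI, measured as the "incidence rate of ARIs (number of episodes of ARI during infancy/total number of children under follow-up". The same section gives two statements about episodes: "we will define each episode of ARI to last for two weeks", and a new episode is counted when "a child who has had no symptoms for at least one week develops signs and symptoms of ARI".

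Section 3.6 (Statistical analysis and reporting) uses ARI in four ways:
- The city comparison forms relative and attributable risk from the "probability of outcome (incidence/proportion) among the high pollution group (exposed) divided by the probability of outcome among the low air pollution group".
- ARI episodes enter as a count only in a Pearson or Spearman correlation.
- Multivariable logistic regression is applied to "health outcomes in binary forms – growth/development/ARI".
- There is also a "logistic regression model of ARI symptoms within a distributed lag nonlinear modeling framework" (DLNM), relating exposure over preceding periods to ARI events.

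Section 2 makes ARI incidence by exposure level the second objective. Section 3.3.1 inflates the sample for exclusions and attrition, while the Discussion expects attrition to be minimal. Section 3.5 plans multiple imputation. The article states no ARI rate, ARI power or post-birth loss rate.

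**The concern.** An incidence rate needs time at risk in its denominator once children are observed for unequal lengths of time. Here it has none, and the wording does not say whether children under follow-up means all who entered infancy follow-up or those still present at a given date. Those readings err in opposite directions.

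The quantity also does not fit the city comparison. A child with three colds contributes three to the numerator and one to the denominator, so the result is a mean count. Relative and attributable risk as described in section 3.6 need a probability.

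The second objective asks for incidence, yet the adjusted regression is logistic, and the count appears only in an unadjusted correlation. At stake are the absolute rate, any attributable risk built on it, and the precision of the adjusted exposure-ARI estimate.

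**Working it through.** The article gives no ARI figure to reproduce, so loss rates, episode rates, dispersion and illness durations below are assumptions shown as ranges.

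**1. Denominator.** Assume a constant episode rate and a proportion d of children lost, evenly over the year. Mean observed time per child is 1 − d/2 years. Relative to the child-time rate, the stated formula gives:
- all children in the denominator: 1 − d/2
- only remaining children in the denominator, all episodes kept: (1 − d/2)/(1 − d)

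| d | All children | Remaining children |
|---|---|---|
| 10% | 0.95 | 0.95/0.90 = 1.06 |
| 20% | 0.90 | 0.90/0.80 = 1.13 |
| 30% | 0.85 | 0.85/0.70 = 1.21 |

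**2. Between-city ratio.** With all children as denominator, the true rate ratio is multiplied by (1 − d₁/2)/(1 − d₂/2):
- equal loss: 1.00, so no distortion
- 20% v 10%: 0.90/0.95 = 0.95
- 30% v 10%: 0.85/0.95 = 0.89

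A rate difference is scaled by the factor in step 1 even when loss is equal.

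**3. Rate against probability.** If m is the mean number of episodes per child, section 3.4.2.3.2 reports m. A probability of at least one episode is 1 − exp(−m) under a Poisson model. At m = 2 these are 2 and 0.86. They are different quantities, so the two sections cannot both be applied to ARI as written. This needs no assumption about the actual rate.

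**4. Binary form, if it means any ARI in the year.** Assume a true rate ratio of 1.25, a negative binomial count with k = 2, 571 children per group and two-sided 5%. For the count model, SE(log ratio) = √[(1/m₀ + 1/k)/n + (1/m₁ + 1/k)/n], with m₁ = 1.25 m₀. For the yes/no outcome, p = 1 − (k/(k + m))^k and the proportions are compared directly.
- m₀ = 1: SE = 0.070 and ln(1.25)/SE = 3.19, power 89%. Yes/no: 0.556 v 0.621, power 62%.
- m₀ = 4: SE = 0.050 and ln(1.25)/SE = 4.43, power 99%. Yes/no: 0.889 v 0.918, power 39%.

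The article does not make clear whether 571 is per city or in total. With 285 per group and m₀ = 4, the powers are 88% and 22%.

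**5. If ARI is recorded as yes/no each month instead.** The share of Poisson information kept is x/(exp(x) − 1), with x the expected episodes per month: 96% at 1 episode a year, 88% at 3 and 77% at 6. A DLNM built on such a series would lose much less than step 4 suggests.

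**6. Episode rules.** Symptoms on days 1-3 and again from day 11 leave seven free days (4-10). A fixed 14-day episode counts one; the symptom-free rule counts two. In simulation with 3, 6 or 9 symptom onsets a year and mean durations of 4 or 7 days, the 14-day count was 0.97 to 1.05 times the symptom-free count.

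**The case against.** A reader might infer three stronger things that the article does not support.

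*Follow-up loss biases the exposure comparison.* Equal loss leaves the between-city ratio intact, and nothing in the article points to differential loss. Most planned withdrawals (pregnancy loss, preterm birth, asphyxia, anomalies) fall at or before birth and cost no infant follow-up time. The Discussion expects minimal attrition, and imputation with a complete-data sensitivity analysis is planned. All of that limits the likely harm. It does not mend a stated formula that lacks time at risk, nor the absolute rate derived from it.

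*Most of the ARI information is discarded.* This would require binary to mean once per child-year and a rate above about 1.26 episodes a year (where the Poisson information kept falls to half). The article says neither. Section 3.4.2.3.2 also classifies ARI by site and severity, so a binary lower-tract or pneumonia outcome need not be near its ceiling, and the logistic DLNM may keep repeated events. What stands is that no adjusted model named in the article estimates the incidence rate.

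*The two episode rules are in outright conflict.* They can be read as an episode length plus a restart rule, both cited to one source. Only the precedence is missing, and the effect on totals is small and can go either way.

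It is also fair to say that model details such as the offset or the dispersion form are commonly left to an analysis plan. The denominator and the probability-based comparison, however, are fixed in the article itself.

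**Conclusion.** The point holds. As written, the ARI measure is a mean count per child with an undefined denominator date, and section 3.6 treats incidence as a probability. For an assumed evenly spread loss of 10-30%, the reported rate would be 5-15% too low or 6-21% too high, depending on which children are counted. Distortion of the city ratio is conditional on unequal loss or timing. The adjusted logistic regression does not answer the incidence question. Its cost in power may be large (99% v 39% at 4 episodes a year) or more modest (89% v 62% at 1), under an assumed rate ratio, dispersion and yearly yes/no reading, and the DLNM may recover much of it. The episode rules need one clarifying sentence. Because ARI is additional to the primary growth and development outcomes, although it is the second objective, severity is moderate.

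**What to change.** - Define the rate as new ARI episodes per child-time at risk, and state how time within an episode is treated.
- Compare cities and exposure levels by rate ratio and rate difference from a negative binomial (or overdispersed Poisson) model with a log child-time offset, adjusted for the listed confounders.
- Keep relative and attributable risk as probability measures only for an outcome explicitly defined as binary, and say what binary ARI means (which class, over what period).
- If repeated ARI indicators enter the DLNM, allow for within-child correlation by a child random intercept or GEE.
- Reconcile the two-week episode length with the one-week symptom-free restart rule by stating which prevails.

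The cost is analysis wording and one definition. The monthly form needs symptom onset and end dates if it does not already capture them; this should be settled before follow-up starts, since such dates are hard to recover later.

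### Growth before birth is indicated only by two cut-points of birth weight; no named analysis takes birth weight as a continuous outcome on prenatal exposure

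*Protocol article*

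**What the plan says.** Section 3.4.2.3.2 (Study outcomes) sets the primary family: "The primary study outcomes are related to childhood growth and development, as shown in Tables 1, 2". In Table 1, two rows carry the label of a proxy for growth before birth, and both are proportions: "Proportion of children diagnosed as SGA at birth (proxy of in-utero growth of the child" and "The proportion of children diagnosed as LBW at birth (proxy of in-utero growth of the child".

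Section 3.6 (Statistical analysis and reporting) states that "multivariable logistic regression model analyses will be used to study the relationship between environmental variables" such as PM and blood metals and "the health outcomes in binary forms – growth/development/ARI". It also plans linear mixed-effects models for "child health outcomes- mean anthropometric data (height, weight, head, and mid-arm circumference" and for developmental level.

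The raw measurement is available. Under Early neonatal period (3.4.2.2.1), staff visit to "collect anthropometric data of the baby (preferably within 72 h of birth", supplementing hospital records, and gestational age at birth is obtained. The child's sex and at-birth weight are listed in section 3.4.2.3.3, where at-birth weight appears under confounders and effect modifiers.

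**The concern.** Size at birth can depend only on exposure before birth, so it is the outcome that isolates the prenatal half of early-life exposure. The plan measures it on a continuous scale but names only yes/no versions as outcomes. If PM or metals shift the whole birth-weight distribution a little, a cut in the lower tail registers only part of that shift, and the test is weaker than the same data allow. At stake is the sensitivity of a primary domain. For a modest effect, an inconclusive LBW or SGA result would say less about in-utero growth than the measured weights could.

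**Working it through.** **1. The plan's own figure.** The only sizing figure is 571 mother-child pairs (section 3.3.1), from 80% power, a two-sided 95% confidence level and an odds ratio (OR) of 1.74 for stunting. The article does not give the baseline stunting rate and refers to a supplementary data sheet, so 571 cannot be reproduced. With continuity correction and equal groups, it fits a baseline of about 8.2-8.7% if 571 is per group, or about 20.2-22.4% if it is the total (mirror solutions at high rates also exist). Enrolment does not settle which: 571/783 = 73% retained, 571/1,566 = 36% retained. Both readings are carried below, as 285 or 571 per exposure group. No power is stated for LBW or SGA.

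**2. What the named analyses cover.**
- City relative and attributable risk: binary outcomes.
- Correlations: growth z-scores, which Table 1 defines as length-for-age, weight-for-age, weight-for-length and BMI-for-age. Birth weight for gestational age is not among them, and simple correlations are unadjusted.
- Logistic regression: binary growth outcomes, hence LBW and SGA.
- Linear mixed models: continuous anthropometry over follow-up. The text does not say whether the birth value is included.
- Distributed-lag models: ARI and growth z-scores over preceding exposure periods. Birth size is not named.

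None names a continuous birth-size outcome on prenatal exposure.

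**3. Information kept by a cut.** Assume normally distributed birth size and a shift in its mean. Efficiency relative to the measured value is φ(z_p)² / [p(1−p)], where p is the rate below the cut. The rates are assumptions.
- 10%: 0.1755²/0.09 = 0.34
- 20%: 0.2800²/0.16 = 0.49
- 30%: 0.3477²/0.21 = 0.58
- 40%: 0.3863²/0.24 = 0.62

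**4. Power of the cut where measured weight has 80%.** With n per group, the shift is d = (1.960 + 0.842)·√(2/n): 0.235 SD for n = 285 and 0.166 SD for n = 571. The exposed rate is p1 = Φ(z(p0) + d). Cut power is Φ{[(p1−p0) − 1.96·√(2p̄(1−p̄)/n)] / √([p0(1−p0)+p1(1−p1)]/n)}.

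| Rate p0 | p1, n = 285 | Power of cut | p1, n = 571 | Power of cut |
|---|---|---|---|---|
| 10% | 0.148 | 41% | 0.132 | 40% |
| 20% | 0.272 | 52% | 0.250 | 52% |
| 30% | 0.386 | 58% | 0.360 | 58% |

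To reach the same power, the cut needs about 2.6-2.8 times the sample at 10%, 1.9-2.0 times at 20% and 1.7 times at 30%.

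**5. If the stunting OR of 1.74 applied to the cut (an assumption).** Here p1 = 1.74·p0/(1−p0+1.74·p0) and d = z(p1) − z(p0). At 10%: p1 = 0.174/1.074 = 0.162 and d = 0.295.

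| Rate p0 | Cut vs measured, 285 per group | Cut vs measured, 571 per group |
|---|---|---|
| 10% | 59% vs 94% | 88% vs over 99% |
| 15% | 73% vs 96% | 95% vs over 99% |
| 20% | 81% vs 97% | 98% vs over 99% |
| 30% | 89% vs 98% | 99% vs over 99% |

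**6. Simulation with a continuous exposure**, as in the section 3.6 regressions: linear against logistic regression, 1,500 runs per setting. For n = 571, power is 80% vs 38% at a 10% rate, 80% vs 50% at 20% and 82% vs 57% at 30%. For n = 1,142 it is 80% vs 35%, 81% vs 49% and 78% vs 54%. The two-group formulas are not what creates the gap.

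**The case against.** The strongest reply is that this is silence in a condensed article. The mixed models use continuous weight and early-life exposure, which the article defines as both pre- and post-natal. The phrase about summed exposure can be read as applying to heavy metals only, which leaves pregnancy-month PM available as a predictor. Nothing excludes the birth value.

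This stands in part. A reader might infer that measured birth weight is discarded, and the documents do not support that: it is collected and may enter the mixed models. But Table 1 does more than stay silent. Its indicator column fixes the in-utero indicators as two proportions, whereas Table 2 names continuous scores for development. A model pooling infancy measurements would not by itself give a birth-size estimate on prenatal exposure.

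Three further inferences go too far:
- That a null LBW or SGA result is likely, or that a shift would be largely invisible to a cut. At OR 1.74 the cut has 59-89% power even with 571 pairs in total (rates of 10-30%).
- That withdrawal of preterm births narrows the birth-weight distribution under analysis. Section 3.3 withdraws them from further follow-up, but birth outcomes are recorded at birth and Table 1 defines LBW regardless of gestational age. The text does not say that they leave the LBW denominator.
- That LBW and SGA should become merely descriptive. The planned city comparison by relative and attributable risk needs binary outcomes.

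It is also fair that OR 1.74 concerns stunting in under-fives, that the rates are assumed, and that 571 is a count after follow-up losses, so an analysis at birth could have more pairs. These affect absolute power. The relative efficiency in step 3 does not depend on the sample size or the OR.

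**Conclusion.** The point holds as a choice of indicator and model that could be better at almost no cost. The only named indicators of growth before birth are two cuts of birth weight analysed as binary outcomes, and no named analysis uses the continuous measurement on prenatal exposure. For an effect that measured weight would detect with 80% power, the cut falls 22 to 40 points short at rates of 10-30%.

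This rests on approximate normality, a location shift, and rates that the article does not give. The practical loss is small if the effect is as large as OR 1.74 and 571 pairs are available per city: under 5 points from a 15% rate upward, though about 12 points at 10%. It is large for smaller effects or if 571 is the total. The sponsor should make the change. The LBW and SGA analyses are not invalid as they stand.

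**What to change.** - **Table 1:** add birth weight in grams and the birth-weight-for-gestational-age z-score, on the same sex-specific reference as SGA, as the in-utero growth outcomes.
- **Section 3.6:** name a linear model of these outcomes on prenatal exposure only (PM2.5, PM10 and maternal blood metals) as the main test of the association between prenatal exposure and birth size. Adjust birth weight for gestational age and sex, and both outcomes for the listed confounders.
- **LBW and SGA:** keep both as reported outcomes, including in the planned relative-risk, attributable-risk and logistic analyses.
- **Mixed models:** state whether the birth measurement enters.

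The cost is wording in two places and one extra linear model per exposure for each outcome. The main effect would be in grams or z-score units, which policy readers may find less direct; the LBW and SGA results remain for them. No new data, visits or participants are needed.
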